### Settings and target population

Municipalities located in the north, middle and south-eastern part of Norway will be contacted to participate in the trial. To ensure collaboration and implementation throughout the trial, we will arrange meetings with the health care leaders in the municipalities and the managers and physicians working in each nursing home. We will strive to recruit nursing homes located in both rural and urban areas of Norway and to obtain an equal distribution of large and small nursing homes to ensure a representative nursing home population. Nursing homes already using TIME as part of their clinical routines will not be invited to take part in the trial.

All patients in wards in participating nursing homes will be considered eligible for inclusion in the trial, and will be assessed to determine if they meet the inclusion criteria. Trained nursing home staff will perform the assessments. The research team will train these staff members on the inclusion procedure and the assessment of patients’ capacity to provide consent. The data obtained from screening individual eligible patients will not be recorded. Patients who fulfil the inclusion criteria and agree to participate will be included in the trial. For patients who lack the capacity to provide consent, written consent will be obtained from their next of kin.

The inclusion criteria for patients are as follows:NH patients with probable dementia, defined as a Clinical Dementia Rating scale (CDR) [16] score of one or higher.A moderate to high degree of agitation, defined by an NPI-NH agitation item score equal to or above six points.Long-term patients who have resided in the nursing home for a minimum of two weeks before inclusion.

The exclusion criterion for patients is a life expectancy of less than 4–6 weeks.

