### Sample size calculation based on the primary outcome

The primary outcome of the trial is the change in the level of agitation from baseline at eight weeks, as measured by the agitation item of the Neuropsychiatric Inventory-Nursing Home Version (NPI-NH) [17, 18]. Power calculation was based on the following assumptions. A previous non-controlled pilot study of TIME showed that the intervention decreased the NPI-NH agitation item score by on average 2.8, with a standard deviation (SD) for change of 3.1 [13]. One can reasonably assume that the simple education-only intervention and baseline and follow-up assessments may have some effect on the control group. Therefore, we expect that the difference in the effect between the control and intervention groups will be lower. We have assumed a mean difference between the groups to be 1.5 as measured by NPI-NH agitation item, and that this difference will have a SD of 3.1. Based on this assumption, we calculate that 65 persons must be included in each group to observe a statistically significant difference with a power of 80 % and a significance level of 5 %. We assume an intra-cluster (nursing home) correlation coefficient (ICC) of 0.05. The ICC is assumed to be low because the persons included will be located in different departments and units in the nursing home (the cluster). Adjusting power calculations for cluster effect, we find that at least 78 persons have to be included in the intervention group and 78 in the control group for the effect to be statistically significant. That is, we need a total of 156 persons. Based on previous studies, we assume that the average size of the nursing homes is 46 patients and that each nursing home will recruit five patients, on average. In the pilot study, we found that approximately 12 % of patients had dementia and an NPI-NH agitation item score of six or higher, which is our main criterion for inclusion. Previous studies have shown that we can anticipate a 30 % loss to follow-up per year (due to, e.g., mortality, relocation, or withdrawal from the study)—that is, 7.5 % in three months. Thus, we will need a total of 168 people (84 persons in each group), indicating that we will need to screen approximately 1400 nursing home patients. Given approximately 46 patients on average per nursing home, we will need to recruit approximately 30 nursing homes. The nursing homes will be randomized after the baseline assessment to avoid bias. The recruitment of new patients to the study will therefore occur only through the recruitment and randomization of new nursing homes, as described above.

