### Randomization

Nursing homes will be stratified by size into three blocks to assure approximately equal number of patients in the two trial arms. Block size will be fixed—block 1: 1–5 patients, block 2: 6–9 patients, and block 3: 10 or more patients. Then, nursing homes within each block will be randomly assigned to either the intervention group or the control group. A researcher will perform the randomization procedure independently of the project management team and the nursing homes. The project management team will provide the nursing homes with the randomization and allocation results immediately following this procedure. Specially trained project nurses who are not affiliated with the nursing homes will assess patients’ baseline characteristics before randomization. These assessors will also assess the effect of the intervention via telephone at weeks eight and 12 and will be blinded to the randomization result.

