### Baseline data and primary and secondary outcome measures

A full description of the screening instruments used to assess the inclusion criteria and the primary and secondary outcomes is provided in Table 3. The primary outcome of the TIME trial is the difference in the change between intervention and control group in agitation/aggression at 8 weeks from baseline, as measured by the NPI-NH [17]. The Norwegian version of the NPI-NH has shown high inter-rater reliability and validity [23].

**Table 3 Tab3:** Primary and secondary outcome measures

What is measured (scales/tools)	Characteristics and psychometric properties of scales/tools
Primary outcome measure: The difference between the intervention group and the control group in change from baseline at 8 weeks	
Agitation/aggression (single item from the NPI-NH)	Change from baseline of agitation and aggression, as defined by the Neuropsychiatric Inventory-Nursing Home version (NPI-NH) item agitation/aggression. The NPI-NH assesses the frequency (0–4) and the severity (0–3) of 12 psychiatric and behavioural symptoms. An item score is generated by multiplying frequency and severity (0–12). A higher score indicates more frequent and severe presence of NPS.
Secondary outcome measures: The difference between the intervention group and control group in change from baseline at 8 and 12 weeks	
Neuropsychiatric symptoms (NPI-NH)	12 items described in the Neuropsychiatric Inventory Nursing Home Version (NPI-NH). Range 0–12, as described above.
Subsyndrome of agitation (NPI-NH)	The NPI-NH subsyndrome agitation is defined as the sum of the scores of the agitation/aggression, irritability, and disinhibition items. Range 0–36.
Subsyndrome affective symptoms (NPI-NH)	The NPI-NH subsyndrome affective symptoms is defined as the sum of the scores of depression and anxiety items of the NPI-NH. Range 0–24.
Subsyndrome psychotic symptoms (NPI-NH)	The NPI-NH subsyndrome psychosis is defined as the sum of the hallucinations and delusions items. Range 0–24.
Neuropsychiatric symptoms (NPI-10 NH sum score)	The NPI-10 NH sum score is the sum of the first ten items in the NPI-NH, omitting the sleep disturbances and eating disorders (primarily vegetative symptoms) items. Range 0–120.
Caregiver occupational disruptiveness (NPI-NH)	In NPI-NH, the caregiver must rate how disruptive they consider each behaviour or symptom on a five-point scale. Range 0–5. A higher score indicates a more disruptive behaviour.

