### Data processing and statistical analysis of quantitative data

All data regarding the cluster randomized trial will be collected via telephone. The data will be registered online in the dataset prepared for the study using the data tool Checkbox via a web survey to the SQL database. The questionnaires used to collect all other data will be distributed to staff (regardless of job position) by mail and the results will be stored in the same manner as the trial data. At the 6- and 12-month assessments, questionnaires will be sent only to the staff who responded to the previous questionnaires.

The data will be presented as frequencies and percentages for categorical and means (standard deviations) for the continuous variables. The normality of continuous variables will be assessed graphically. If necessary, skewed data will be transformed. Differences in the changes in outcomes between the intervention group and the control group will be assessed by a linear mixed model with fixed effects for time component and group and the interaction between the two. A significant interaction will imply the differences in change between the groups. Random effects for patients nested within nursing homes and slopes (if significant) will be included into the model. Individual time point contrasts will be derived within each group at each time point with the corresponding 95 % confidence intervals and *p*-values. Linear mixed model correctly adjusts estimates for intra-cluster correlations as well as for intra-individual correlations due to repeated measurements in time. The model also handles unbalanced data by allowing inclusion of all available information, also from drop-outs.

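### The primary model compares raw change and leaves the pre-randomization baseline score unadjusted, forgoing precision that is available at no cost

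*Protocol article*

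**What the plan says.** The section on data processing and statistical analysis specifies "a linear mixed model with fixed effects for time component and group and the interaction between the two", and adds: "A significant interaction will imply the differences in change between the groups". On random effects it says: "Random effects for patients nested within nursing homes and slopes (if significant) will be included into the model". It lists neither a baseline covariate, nor a common baseline mean, nor a size stratum.

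The primary outcome, under baseline data and outcome measures, is "the difference in the change between intervention and control group in agitation/aggression at 8 weeks from baseline". The sample size section assumes a "mean difference between the groups to be 1.5 as measured by NPI-NH agitation item, and that this difference will have a SD of 3.1"; the 3.1 comes from the pilot's SD of change. The same section and the Randomization section place the baseline assessment before randomization. Randomization is stratified: "Nursing homes will be stratified by size into three blocks to assure approximately equal number of patients in the two trial arms", with limits "block 1: 1–5 patients, block 2: 6–9 patients, and block 3: 10 or more patients". Patients enter with "A moderate to high degree of agitation, defined by an NPI-NH agitation item score equal to or above six points".

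**The concern.** With group, time and their interaction all free, baseline is one of the repeated outcomes and each arm has its own baseline mean. With complete data the week-8 interaction contrast is then the difference between arms in mean raw change, so each patient's baseline score is subtracted with weight 1, whatever its actual relation to the week-8 score. Because homes are randomized after baseline, the expected baseline means are equal, and the analysis may use that fact. If the slope of week-8 score on baseline is below 1, subtracting the whole baseline score adds noise. At stake is some power in a trial whose planned power has little slack.

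**Working it through.** **The plan's own figure.** Two-sided 5%, 80% power, difference 1.5, SD 3.1: n = 2 × (1.960 + 0.842)² × 3.1² / 1.5² = 67.05, so 68 per group; the plan states 65. At 65 per group the SE is 3.1 × √(2/65) = 0.544 and power is 78.8%. The later steps follow from 65: the design effect is 1 + (5 − 1) × 0.05 = 1.2, 65 × 1.2 = 78 per group, 156 in total, and 156 × 1.075 = 168.

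**Power of the stated model at the planned size.** 168 × 0.925 / 30 = 5.18 patients per home, so the design effect is 1 + 4.18 × 0.05 = 1.209. With 84 × 0.925 = 77.7 patients per arm, SE = 3.1 × √(2 × 1.209 / 77.7) = 0.547. Power = Φ(1.5/0.547 − 1.96) = 78.3%.

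**Effect of adjusting for baseline.** Let s0 and s1 be the baseline and week-8 SDs. The change SD of 3.1 fixes the correlation:

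- r = (s0² + s1² − 9.61) / (2 × s0 × s1)
- slope b = r × s1 / s0
- adjusted variance = s1² × (1 − r²), compared with 9.61 for raw change

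The documents do not give s0 and s1. The ranges below are assumptions. Entry at 6 or more on an item scored as frequency times severity allows only 6, 8, 9 and 12; equal weights on these give an SD of 2.17, so values near 2.2 are reasonable for s0. The same design effect is assumed for both analyses.

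| s0 | s1 | r | b | adjusted variance | ratio to 9.61 | power |
|---|---|---|---|---|---|---|
| 1.8 | 3.5 | 0.47 | 0.91 | 9.58 | 0.997 | 78% |
| 2.5 | 3.5 | 0.51 | 0.71 | 9.09 | 0.946 | 81% |
| 2.2 | 3.2 | 0.39 | 0.57 | 8.69 | 0.905 | 82% |
| 1.8 | 2.8 | 0.15 | 0.23 | 7.67 | 0.798 | 87% |
| 2.5 | 2.8 | 0.32 | 0.36 | 7.04 | 0.732 | 89% |

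As a second route, fix the change SD at 3.1 and s0 at 2.0. The ratio is then 1 − (1 − b)² × s0² / 9.61. Slopes of 1, 0.75, 0.5 and 0.25 give 1.00, 0.97, 0.90 and 0.77. With 78 per arm and design effect 1.2, power is 78.8%, 79.8%, 83.0% and 88.3%.

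**Chance imbalance.** At 2.2/3.2, with 84 per arm and an ICC of 0.05 assumed for baseline too, the SE of the baseline difference is √(2 × 2.2² × 1.2 / 84) = 0.37. A difference of 0.5 or more would occur in about 18% of trials. Given a 0.5-point imbalance, raw change is off by 0.5 × (1 − 0.565) = 0.22 points. This is the same variance component as in the table, viewed conditionally; it is not an additional error.

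**Strata.** Generalized least squares on an assumed layout (30 homes in three size strata, complete data, random home intercept) gives an SE of 0.4621 for the week-8 interaction, with or without a stratum main effect. Only the equality matters here; the level depends on the layout.

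**Form of the fix.** A common-baseline model with random intercepts only weights baseline by one common correlation. With 1.8/3.5 and assumed week-8 to week-12 correlations of 0.5 to 0.9, its variance is 7% to 3% higher than for raw change. With 2.2/3.2 it is still 8% to 10% lower.

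**The case against.** The strongest reply is that nothing here is an error. Outcome definition, power basis and test all concern the difference in change, and the stated analysis is unbiased. The size of the gain depends on SDs that the documents do not give, and the range starts at no gain. All of this stands, and it makes the point a recommendation on efficiency rather than a correction.

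Four stronger readings are tempting, and the documents support none of them.

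- *Planned precision is lost.* It is not. The 3.1 is already an SD of change, so the stated model delivers the power that was planned, and only extra precision is forgone.
- *Selecting scores of 6 or more makes raw change especially inefficient.* The reverse holds. Under a linear regression, selection on baseline leaves b and the residual variance unchanged, and the penalty for raw change is (1 − b)² × s0². With b = 0.565 and residual variance 8.69, the variance ratio is 0.79 at s0 = 3.5, 0.905 at 2.2 and 0.93 at 1.8.
- *Regression to the mean biases the comparison.* It is expected equally in both arms because baseline precedes randomization, and it cancels from the contrast in expectation.
- *Omitting the strata costs precision or validity.* A stratum main effect cancels from the stated interaction contrast. The stated purpose of the strata is balance in patient numbers, nothing shows size to be prognostic, and omitting strata normally makes inference conservative. A condensed article may also leave the term to an analysis plan.

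**Conclusion.** The point holds as an efficiency recommendation. The stated primary analysis is a valid, unadjusted comparison of mean change. Adjusting for the pre-randomization baseline score keeps the same estimand and is asymptotically never less precise, provided that the slope on baseline is estimated freely. The gain is 0 to 27% in residual variance, or power of 78% to 89% against about 78%; the middle case is 10% and about 82%. It rests on the stated change SD of 3.1, the assumed ranges for the baseline and week-8 SDs, and the same design effect for both analyses. It vanishes as the slope on baseline approaches 1. The middle case would bring power back above the nominal 80%, which the stated 65 per group does not quite reach.

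**What to change.** Model the 8- and 12-week scores with baseline score as covariate, fixed effects for time, group and time × group, and random effects for patient within nursing home. Equivalently, keep all three visits and fit a common baseline mean for both arms with an unstructured within-patient covariance. Random intercepts alone are not enough for that version, because they do not guarantee a smaller standard error.

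As a secondary point, include the three-level size stratum as a fixed effect in the adjusted model, so that the analysis reflects how homes were randomized.

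The cost is one line in the model and no extra patients or data. The stratum takes two between-home degrees of freedom; with 30 homes the critical t value moves from 2.048 (28 df) to 2.056 (26 df). The choice should be fixed before outcome data are seen by arm.

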**Methods/design:**

The trial is a 3-month cluster randomized trial conducted in 30 nursing homes including 168 participants with dementia and a high level of agitation. Each nursing home defined as a cluster will be randomized to receive either the TIME intervention (the intervention group) or a brief education-only intervention regarding dementia and NPS (the control group). TIME is a manual-based, multicomponent programme that includes a rigorous assessment, one or more case conferences and the treatment and evaluation of NPS. Patient-level measurements are taken at baseline (prior to randomization) and 8 and 12 weeks later. The primary outcome measure is the change in agitation, as defined by the Neuropsychiatric Inventory-Nursing Home Version, at 8 weeks from baseline. Secondary outcome measures include change in agitation at 12 weeks from baseline, and change from baseline at 8 and 12 weeks in other NPS, quality of life, and the use of psychotropic and analgesic medications. Mixed methods will be used to follow, measure and explore the implementation process and the effect of the intervention at the individual staff level and the organization level. Combining measurements of clinical effectiveness and implementation outcomes define this trial as an effectiveness-implementation hybrid trial.

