Agitation (CMAI)	The Cohen-Mansfield Agitation Inventory (CMAI), which measures 29 different types of agitation and the frequency at which they occur. Range for each item 1–7. Range total score 29–203. A higher score indicates more frequent agitation. Good validity and inter-rater reliability.
Depressive symptoms (Cornell)	The Cornell Scale for Depression in Dementia, which measures the frequency of symptoms of depression.
Quality of life (QUALID)	Quality of Life in Late-stage Dementia Scale, which measures 11 behaviours rated on a 5-point Likert scale. Range 11–55. A lower score indicates higher quality of life. Good validity and inter-rater reliability
Use and dosage of psychotropic and analgesic medication (defined as daily dosage (DDD))	Psychotropic and analgesic medication given both regularly and on demand. This will be assessed using a questionnaire and extracted from patients’ records. The assessment of the medication given on demand will be obtained from patients’ records at each visit and presented as the sum in mg used for the last 21 days. These drugs will be grouped according to the Anatomical Therapeutic Chemical Index.

The secondary outcomes include the difference in the change between the two groups in agitation/aggression at 12 weeks from baseline, as measured by the NPI-NH, in the change from baseline to 8 and 12 weeks in each of the other items of the NPI-NH, the NPI-NH 10 sum score, NPI-subsyndromal agitation score (aggression/agitation + disinhibition + irritability), NPI-subsyndromal psychosis score (delusion + hallucination) and affective symptoms (depression + anxiety). These subsyndromes are based on data from a previous principal component analysis [24]. The other secondary outcomes include the difference between the two groups in the change from baseline to 8 and 12 weeks in the following measures: agitation, as measured by the Cohen-Mansfield Agitation Inventory (CMAI; [25]; symptoms of depression, as measured by the Cornell Scale for Depression in Dementia (CSDD); [26, 27]; drug use and dosage of psychotropic and analgesic medications given both regularly and on demand, coded as defined daily dosage (DDD) and grouped according to the Anatomical Therapeutic Chemical index [28]; and quality of life, as measured by the Quality of Life in Late-stage Dementia Scale (QUALID); [23, 29].

### Qualitative and quantitative methods employed in the trial to answer research questions 2 and 3

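### The analysis section does not name the between-group week-8 contrast as the primary test; it gives an interaction with no time point, plus within-group contrasts

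*Protocol article*

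**What the plan says.** The protocol article is consistent about the outcome. The section on baseline data and outcome measures gives the primary outcome as "the difference in the change between intervention and control group in agitation/aggression at 8 weeks from baseline"; Table 3 and the abstract agree. The same section places week 12 lower: "The secondary outcomes include the difference in the change between the two groups in agitation/aggression at 12 weeks from baseline". The sample size section plans for one two-group comparison of change: "We have assumed a mean difference between the groups to be 1.5 as measured by NPI-NH agitation item".

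There are three visits. The abstract states: "Patient-level measurements are taken at baseline (prior to randomization) and 8 and 12 weeks later".

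The section on data processing and statistical analysis assigns differences in change between the arms to "a linear mixed model with fixed effects for time component and group and the interaction between the two". It continues: "A significant interaction will imply the differences in change between the groups". It does not say how time is coded, which interaction term is meant, or whether the terms are read jointly or one by one. It allows random slopes if they are significant. The time-specific results it promises, with confidence intervals and p-values, are these: "Individual time point contrasts will be derived within each group at each time point".

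**The concern.** With three visits, the time-by-group interaction is not one number. If time is categorical, it has two terms, one for week 8 and one for week 12, and its overall test has 2 df. That test mixes the primary outcome with a secondary one. If time is linear, the interaction is a difference in slopes, which forces the week-8 effect to be 8/12, or two thirds, of the week-12 effect. The singular time component and the optional random slopes keep the linear reading open. Neither overall test is the week-8 difference in change for which the trial is sized.

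The listed contrasts do not close the gap, because a within-group contrast does not compare the arms. Patients enter with an agitation item score of six or more, so both arms can be expected to fall by regression to the mean. The sample size section itself expects that the control arm may improve somewhat. A significant fall within one arm therefore says little about the intervention.

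At stake is the trial's main conclusion. Several tests fit the text, they can disagree, and the text does not say which one answers the primary question.

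**Working it through.** **Inputs from the protocol article.** Difference 1.5, SD of change 3.1, power 80%, significance level 5%, ICC 0.05, five patients per home on average, 7.5% loss, visits at 0, 8 and 12 weeks.

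**Assumptions not in the document.** Two-sided test; SD 3.1 for both changes; correlation r between the 8- and 12-week changes of 0.3 to 0.7, with 0.9 as a further check.

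**1. The plan's own sample size.** For one two-group contrast, n = 2 × [3.1 × (1.960 + 0.842) / 1.5]² = 67.05, so 68 per group. The plan states 65, which gives 78.8% power. From 65 the later steps follow: design effect 1 + (5 − 1) × 0.05 = 1.2; 65 × 1.2 = 78; 2 × 78 = 156; 156 × 1.075 = 167.7, so 168. The small gap between 65 and 68 is a separate matter. What counts here is that the sample size rests on a single 1-df contrast.

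**2. Categorical time, joint 2-df test.** At the planned 80% power, one contrast of 1.5 points has non-centrality L = (1.960 + 0.842)² = 7.85. If the true effects at weeks 8 and 12 are a and b, in units of 1.5 points, the joint test has non-centrality

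λ = L × (a² − 2r·a·b + b²) / (1 − r²),

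and is compared with the 5% critical value of chi-square on 2 df, 5.99. For a = 0, b = 1 and r = 0.5, λ = 7.85 / 0.75 = 10.47, and the chance of significance is 83%.

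| True effect, week 8 / week 12 | r = 0.3 | r = 0.5 | r = 0.7 | 1-df week-8 test |
|---|---|---|---|---|
| 0 / 1.5 | 75% | 83% | 95% | 5% |
| 1.5 / 0.75 | 73% | 71% | 74% | 80% |
| 1.5 / 1.5 | 88% | 83% | 78% | 80% |

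At r = 0.9 the three rows give over 99%, 94% and 73%. With 65 effective patients per arm (78 / 1.2) in place of exact 80% power, L = (1.5 / 0.544)² = 7.61, and the table entries fall by about 1 to 2 points; the first row becomes 74%, 82% and 94%.

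**3. Linear time.** The least-squares slope through visits 0, 8 and 12 has mean time 20/3 and sum of squares 74.67. A constant 1.5-point effect at both follow-up visits gives a slope difference of [(8 − 6.67) × 1.5 + (12 − 6.67) × 1.5] / 74.67 = 10 / 74.67 = 0.1339 per week. The implied week-8 effect is 8 × 0.1339 = 1.07, which is 29% below 1.5. An effect of 1.5 at week 12 only gives 8 × (5.33 × 1.5) / 74.67 = 0.86 at week 8, where the true value is 0.

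**4. Categorical time, single term.** With baseline as reference, the group-by-week-8 coefficient is the between-group difference in change from baseline to week 8. Its 1-df test is the one that the sample size assumes.

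**The case against.** The strongest reply is that the outcome, its time point, the comparison and the model are all fixed and consistent, and that the coding of time and the reading of the interaction are details for a full analysis plan. The sentence on a significant interaction can be taken as a general explanation for all outcomes at both visits. Much of this stands. Two stronger readings are therefore not supported:

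- A reader might infer that the week-8 comparison is never tested. The text assigns between-group differences in change to the mixed model, and with categorical time that model contains the week-8 term. The primary test is left unidentified; it is not excluded.
- A reader might infer that the interaction, together with the within-group contrasts, is a declared rule for success. The article does not call it one and gives the within-group contrasts no part in a decision.

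Nor does the joint test always cost power. With 1.5 points at both visits it has 78 to 88% power for correlations of 0.7 down to 0.3, so it can do better than the single contrast. The 75 to 95% figure needs an effect absent at week 8 and full at week 12, and the 29% shrinkage needs linear time, which the text does not state.

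What the reply does not remove is that the article does state how the arms are compared. That statement has no time point, and the only time-specific contrasts spelled out are of the wrong kind for the primary question.

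**Conclusion.** The point holds as a failure to identify the primary test. The section that defines the outcome and the section that sizes the trial both point to a 1-df between-group contrast at week 8; the analysis section does not name it.

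The main consequence is that an overall interaction can be significant because of week 12 alone, against 5% for the week-8 contrast when there is no week-8 effect. This rests on the joint reading, equal SDs at both visits and an assumed correlation. Power for a real week-8 effect may be lower or higher than the planned 80%, depending on the effect pattern and the correlation, so a general loss of power should not be claimed. The bias under linear time applies only if time is coded that way.

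This does not undermine the design or the choice of model. It is an improvement available at no cost.

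**What to change.** In the section on data processing and statistical analysis, state that:

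- time is categorical (baseline, 8 and 12 weeks);
- the single primary test is the between-group difference in change from baseline to week 8 in the NPI-NH agitation item (the group-by-week-8 term, 1 df), two-sided at 5%, reported with its 95% confidence interval;
- the between-group difference in change at week 12 is secondary;
- the overall interaction does not decide the primary outcome;
- within-group changes are reported as description, without p-values.

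The cost is a few sentences. The model and data are unchanged, and no new sample size is needed, because this is the comparison that the power calculation already assumes. If a full analysis plan exists, it should carry the same wording, fixed before the outcome data are seen by arm.

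### Keeping random slopes only if significant can leave the week-8 change contrast without the between-home clustering (ICC 0.05) that the trial was sized for

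*Protocol article*

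**What the plan says.** In the protocol article, *Sample size calculation based on the primary outcome* defines the endpoint as a change: "The primary outcome of the trial is the change in the level of agitation from baseline at eight weeks". The variability is also that of a change, taken from the pilot "with a standard deviation (SD) for change of 3.1". For clustering it states: "We assume an intra-cluster (nursing home) correlation coefficient (ICC) of 0.05". The number per group is raised on that basis from 65 to 78.

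*Data processing and statistical analysis of quantitative data* tests the interaction of time and group in a linear mixed model. On the random part it says: "Random effects for patients nested within nursing homes and slopes (if significant) will be included into the model". It then asserts: "Linear mixed model correctly adjusts estimates for intra-cluster correlations as well as for intra-individual correlations due to repeated measurements in time".

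**The concern.** The effect of interest is a difference between groups in change over time. A home random intercept describes homes whose level of agitation is higher or lower throughout. It does not describe homes whose patients improve more or less than those of other homes. Only a home-level slope or a home-by-time effect does that, and the plan makes the slopes conditional on a significance test.

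An ICC of 0.05 on the change outcome says that changes are expected to cluster by home. If the term that carries this clustering is dropped because about 30 small homes cannot show it to be significant, patients in one home are treated as independent with respect to change. The standard error of the primary contrast is then too small, the interval too narrow, and the 5% level not held. Clustering of change is plausible here: each home's own staff deliver the care, and the outcome comes from telephone interviews with staff of the home.

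**Working it through.** **Inputs from the article.** Difference 1.5, SD of change 3.1, 5% level, 80% power, 65 per group before clustering, ICC 0.05, five patients per home on average, about 30 homes, 168 patients in total (168/30 = 5.6 per home), size strata 1-5, 6-9 and 10 or more, assessments at weeks 0, 8 and 12.

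**Assumptions not in the article.** Two-sided test; coefficient of variation (CV) of home size 0 to 0.6; time pattern of home effects; for the three-level simulation, intercept SDs of 0.6 (home) and 1.5 (patient).

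**1. The plan's own figure.** Design effect = 1 + (m − 1) × ICC = 1 + 4 × 0.05 = 1.20, and 65 × 1.20 = 78, as stated. So the ICC was applied to the change outcome. (From 1.5 and 3.1, a two-sided calculation gives 68 rather than 65, with 78.8% power at 65. This does not bear on the present point.)

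**2. What the intercept does to the contrast.** For patient i in home h, write the score at time t as fixed part + u_h + b_hi + w_ht + e_hit, where u_h is the home intercept, b_hi the patient intercept and w_ht a home effect that varies with time. Then

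change = (fixed change) + (w_h8 − w_h0) + (e_hi8 − e_hi0).

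Both intercepts cancel, exactly so with complete data. If w_ht is not in the model, the standard error has no between-home component of change.

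**3. Type I error with no home-level term on change.** The variance is understated by the design effect (DEFF), so actual alpha = 2 × [1 − Φ(1.96/√DEFF)], with DEFF = 1 + [(1 + CV²)m − 1] × ICC.

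| m | CV | ICC of change | DEFF | Alpha |
|---|---|---|---|---|
| 5 | 0 | 0.01 | 1.04 | 5.5% |
| 5 | 0 | 0.05 | 1.20 | 7.4% |
| 5.6 | 0 | 0.05 | 1.23 | 7.7% |
| 5.6 | 0.4 | 0.05 | 1.275 | 8.3% |
| 5.6 | 0.6 | 0.05 | 1.331 | 8.9% |
| 5 | 0 | 0.10 | 1.40 | 9.8% |

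**4. Type I error under the rule as written, taking the slope to be at home level.** A three-level REML model was simulated under the null (30 homes of 5, weeks 0, 8 and 12, SD of change 3.1, ICC of change 0.05, at least 4,000 replicates per run), with a likelihood-ratio test deciding whether the home slope is kept. The ranges cover repeated runs and two versions of the test.

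| Home effects over time | Slope kept | Alpha under the rule |
|---|---|---|
| Independent at each visit | about 12% | 6.9-7.7% |
| Step after baseline | 38-39% | 6.5-7.5% |
| Linear in time | 72% | 4.6-5.7% |

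Intercepts only gave 6.8-8.2% in the same runs. With a true ICC of zero (step structure), the rule gave 5.4-5.5%.

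A simpler simulation on change scores, with an F-test as the pre-test and homes of 5-6, gave 7.2-7.8% for intercepts only and 6.2-6.5% under the rule. The home term was kept in 21-26% of trials.

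**5. When between-home variation in change is always carried.** The change-score simulation gave 5.0-5.2% on 28 df (30 homes − 2 groups). In the three-level simulation at ICC 0.05, a cluster-level t-test of change gave 4.2-5.4%, and a linear home slope always kept gave 3.9-6.1%. The upper end of the last range came from home effects independent by visit, which a linear slope fits only in part.

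**The case against.** The strongest reply is that the plan is not an intercepts-only model. It allows slopes, its sentence names nursing homes as a level, and a retained home-level slope does enter the change contrast. A reader might infer that the primary test ignores clustering outright and that its type I error must exceed 5%. The article does not support that. The result depends on whether the term is kept, and with home effects linear in time the procedure is close to nominal.

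A reader might also infer that the term will nearly always be dropped. Retention at ICC 0.05 ran from about 12% to 72% depending on the time pattern, so no single figure can be given.

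The ICC of 0.05 is an assumption, which the article argues to be low. At 0.01 the excess is half a percentage point even with intercepts only. The article gives no CV of home size and no ICC for any secondary outcome, so the 8-9% figure is conditional and no size can be put on the effect for the secondary outcomes.

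Finally, the level of the slopes and the degrees of freedom are details that an article may leave to the analysis plan, and their absence is no fault.

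All of this limits the size of the problem. It does not remove it, because the article is not silent: it states a data-driven rule for the random effects and asserts that the model adjusts correctly. An analysis plan that follows the rule inherits the defect.

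**Conclusion.** The point holds in conditional form. Unless a home-level effect on change is retained, the week-8 contrast omits the clustering that the sample size assumed, so the assertion of correct adjustment is not assured. At an ICC of change of 0.05:

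- with no home-level term on change, type I error is about 7-8%, or about 8-9% with unequal homes (CV 0.4-0.6 assumed);
- under the written rule it is about 6-8%, falling to about 5% if home effects are linear in time;
- if the true ICC is near zero, there is little or no excess.

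These figures rest on a two-sided test, about 30 homes of 5 to 6 patients, and the assumed time patterns and intercept variances. If the slopes are meant at patient level only, clustering of change is never carried and the first line applies. The excess is moderate, but it falls on the primary test and comes from a stated rule, so it should be corrected before analysis.

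**What to change.** Delete the significance condition. Always include a nursing-home-level random effect on change (home-by-time) beside the patient effect, whatever its estimated size or p-value, and use small-sample degrees of freedom (Kenward-Roger or Satterthwaite, about 28). Limit the statement on intra-cluster correlation to a model that contains this term.

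Two valid alternatives are a cluster-level analysis of change, or a baseline-adjusted model with a random home effect. Neither is equivalent to the planned model. The baseline-adjusted model conditions on baseline, and if fitted to week 8 alone it gives up the week-12 data and patients without a week-8 score.

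The cost is one line of model specification and wider intervals than intercepts alone would give:

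- design effect 1.2: √1.2 = 1.095, about 10% wider, which the sample size already allows for;
- with 28 df as well: 1.095 × 2.048/1.96 = 1.14, about 14% wider;
- with unequal homes too (m = 5.6, CV 0.6): √1.331 × 2.048/1.96 = 1.21, about 21% wider.

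The sample size calculation shows no allowance for the second and third.
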